**Methods/Design:**

A randomized controlled trial (RCT) nested within a 13-month longitudinal cohort study. The RCT (conducted over 12 months) tests the effectiveness of a novel, early, home-based, personalized program (compared with no intervention) in arresting or slowing FD.

TRIIFL focuses on older adults living independently in the community, who have not yet had a serious health event, yet are potentially on the cusp of FD. Participants in the longitudinal cohort study will be recruited as they present to one large tertiary hospital Emergency Department, providing they are not subsequently admitted to a ward. Sample size calculations indicate that 570 participants need to be recruited into the longitudinal study, with 100 participants randomized into the trial arms.

Measures from all subjects will be taken face-to-face at baseline (recruitment), then subsequently by telephone at one, four, seven and thirteen months later. Measures include functional abilities, quality of life, recent falls, mobility dependence, community supports and health service usage. Specific to the nested RCT, the quality of life tool (SF12) applied at one month, will identify individuals with low mental component quality of life scores, who will be invited to enter the RCT.

Assessors will be blinded to RCT arm allocation, and subjects in the RCT will be blinded to the intervention being received by other subjects.

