## Study aim

1. To determine whether an individualized early intervention for community-dwelling older people with poor mental component quality of life scores measured one month after discharge directly from a hospital emergency department (ED), reduces their likelihood and/or rate, of functional decline (FD) over the next twelve months.

2. To demonstrate that:

a. Incipient FD in an older person can be identified within four weeks of discharge from an ED presentation for a minor health event, using lower than median mental component quality of life scores; and

a. Engaging these older people early, into a person-centered home-based intervention, arrests or reduces the rate of FD over the next 12 months.

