### Study 1 analysis

FD will be assessed as change from baseline at each time point as:

•One or more falls increase from the baseline rate

•More than one event of hospitalization, or ED presentation, from the baseline rate

•Decrease of one point in any item of the ADL instrument [18], or

•Decrease of 2+ points from baseline total iADL score [19], or any decrease in baseline score in the domains of home activities, doing laundry, shopping and getting places (we previously reported these domains as critical to functional independence) [37]

•Scores decreasing from above median at baseline in either physical or mental domain, to below median in the SF12 [41,42]

•Any decrease in AQoL_4D (in the manner recently described for chronic obstructive pulmonary disease (COPD))[44]

•Change to a more assistive gait aid (for example, a one point stick to a four-pronged stick)

•Change in living arrangements to more supported care

•Increased carer involvement

•Greater type and frequency of use of formal community services or informal supports

•More frequent GP attendances.

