### Study 2: nested RCT

#### Subject selection and randomization

All participants in Study 1 will be stratified at one-month telephone follow-up into low and high scores on the MCS domain of the SF-12, (SF12-MCS), using the median cut point. We previously reported this as a transformed score of 55 [37], which is comparable to the same age-gender population SF-12 norms [41]. The nested RCT will be conducted involving only the subjects with lower than median SF12-MCS scores at this time point (Figure 1).

An independent trials office will randomize these subjects using a computer generated random number series, into an individualized person-centered community-based intervention, or ‘usual care’ which reflects no intervention. It is unlikely that any intervention would normally be offered to this population as it is not current practice to screen people for low mental component quality of life scores after an ED contact.

Considering Studies 1 and 2, there are three study cohorts (Figure 1):

•Subjects with SF12-MCS scores ≥55, who will be observed only, for 13 months after recruitment (12 months after the one month SF12 scores are taken) (the observed cohort)

•Subjects with SF12-MCS scores <55, from which two RCT groups will be allocated one month after recruitment, randomized into

•Intervention specifically tailored to address the individual’s problems, concerns, and goals (low SF12-MCS, intervention cohort)

•No treatment (low SF12-MCS, no treatment cohort).

Outcome measures for the two RCT groups will be taken at three-, six- and twelve-month time points after randomization (four, seven and thirteen months post-recruitment).

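### Functional decline is measured from the ED interview, a month before MCS selection and randomisation, and one of its SF12 criteria overlaps with the Aim 2a predictor

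*Protocol article*

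**What the plan says.** All references are to the protocol article.

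- **Reference point.** The *Study 1 analysis* section states: "FD will be assessed as change from baseline at each time point as", followed by eleven criteria. The abstract fixes what baseline means: "Measures from all subjects will be taken face-to-face at baseline (recruitment), then subsequently by telephone at one, four, seven and thirteen months later".
- **SF12 criterion.** One of the eleven is "Scores decreasing from above median at baseline in either physical or mental domain, to below median in the SF12". The section does not say which median is meant.
- **Selection and allocation.** The section *Subject selection and randomization* sets out the split as follows: "All participants in Study 1 will be stratified at one-month telephone follow-up into low and high scores on the MCS domain of the SF-12", at the median. For that cut, "We previously reported this as a transformed score of 55". The trial population is "Subjects with SF12-MCS scores <55, from which two RCT groups will be allocated one month after recruitment".
- **Aim 2a.** Incipient FD is to be identified "using lower than median mental component quality of life scores" within four weeks of discharge.
- **Hypothesis 2.** The untreated low-MCS cohort is expected to show FD over the following three months, judged against its status at recruitment.
- **Use of month 1.** *Analysis of data from Studies 1 and 2* compares the cohorts at allocation for homogeneity, then plans repeated-measures ANOVA on each outcome. Nothing re-bases FD to month 1.

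**The concern.** The trial has two starting points. Selection, allocation and RCT follow-up run from month 1, while FD runs from the ED. Whatever happens between the two interviews enters the RCT outcome although no treatment has been given.

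The ED interview is also an awkward anchor. It is face-to-face and the later ones are by telephone. The background section *How is FD detected?* itself questions how valid and reliable an FD assessment is when older people are unwell in an ED.

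The SF12 mental criterion raises a further problem because it uses the same score as the selection rule. In the RCT, month-1 position relative to the median is the same for everyone by design. For Aim 2a, being below the median at month 1 is the predictor, and falling below the median is one of the outcomes. The claim that low MCS identifies decline could then be partly true by construction.

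**Working it through.** **Inputs.** From the article: the ED baseline; contacts at months 1, 4, 7 and 13; selection on MCS below 55 at month 1; allocation at month 1. Not given, and therefore assumed: the correlation r of MCS between visits, the same median cut at each visit, normal scores, and no true change in the mean. The article states no figure to reproduce on this point.

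**Step 1, time span of Hypothesis 2.** No contact falls at three months from recruitment, so its three-month assessment is the month-4 contact. From randomisation that is 4 − 1 = 3 months. From recruitment status it is 4 − 0 = 4 months, the first of them before randomisation.

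**Step 2, the mental criterion crossed with the selection rule.** Every RCT participant is below the cut at month 1.

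| ED score | RCT participant at month 1 | Months 4, 7, 13 |
|---|---|---|
| Above the cut | Criterion already met | Met or not met, depending on whether the score recovers |
| Not above the cut | Not met | Can never be met |

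The observed cohort (55 or higher at month 1) cannot meet the criterion at month 1.

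**Step 3, size.** For a bivariate normal score split at the median, P(above in ED, given below at month 1) = arccos(r)/π.

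| Assumed r | Already met at randomisation | Can never meet |
|---|---|---|
| 0.3 | 40% | 60% |
| 0.5 | 33% | 67% |
| 0.7 | 25% | 75% |
| 0.85 | 18% | 82% |

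**Step 4, later visits.** Scores at months 0, 1 and 4 were simulated (2 million draws, no true change), with either equal correlations between all visits or correlations that decay with each visit (r between adjacent visits, r² from month 0 to month 4).

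| r and structure | Month-4 rate, low-MCS | Month-4 rate, observed | Already met at month 1, back above the cut at month 4 |
|---|---|---|---|
| 0.5, equal | 16.7% | 16.7% | 50% |
| 0.5, decaying | 20.9% | 21.0% | 37% |
| 0.7, equal | 12.6% | 12.7% | 50% |
| 0.7, decaying | 16.8% | 16.8% | 34% |

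Over r from 0.3 to 0.85, month-4 rates run from about 9% to 24% and are about equal in the two cohorts, and 31% to 50% revert. The equality relies on the ED-to-month-1 and month-1-to-month-4 correlations being the same. It shows that a cohort difference at month 4 is not forced, not that none could arise.

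**Step 5, noise.** With equal variances σ², a change score to month 4 has variance 2σ²(1 − r²) from the ED and 2σ²(1 − r) from month 1 under decaying correlations. The ratio is 1 + r, that is 1.5 to 1.7 for r of 0.5 to 0.7. Under equal correlations the ratio is 1. The added noise therefore depends on the ED score predicting later scores less well than the month-1 score does.

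**Step 6, re-basing alone.** If the mental criterion were counted from month 1, every RCT participant would start below 55 and none could meet it. Moving the baseline does not repair this rule.

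**The case against.** The strongest reply is that randomisation takes care of the first month. Change before allocation is balanced between arms in expectation, so for continuous outcomes the expected arm difference is the same from either baseline. The eleven-item list stands under Study 1, and the planned repeated-measures ANOVA on each outcome does not need the yes/no rules. The pilot finding behind Aim 2a defined FD by iADL, falls and hospitalisations, so the predictive idea did not arise from the MCS overlap. All of this stands. It does not remove the point, because the article gives no other FD definition and Hypothesis 2 applies the ED anchor to an RCT arm.

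Three stronger readings are tempting, and the document does not support them.

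- **The mental criterion is fully decided before randomisation.** FD is assessed at each time point, so a participant who already meets it can recover above the cut, and treatment could influence that. Only those not above the cut in the ED are locked out, and even that needs a common cut, which the *Study 1 analysis* section does not confirm.
- **Aim 2a is circular throughout.** The overlap is exact at month 1 and in an ever-met count, which the article does not specify. It is not automatic at months 4, 7 and 13.
- **A month-1 baseline would bring a definite gain in power.** The article gives neither standard deviations nor correlations, and the planned repeated-measures model already uses within-person correlation.

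A further objection concerns the remedy and is right. Table 1 records falls over twelve months and hospitalisations over six months at baseline, but each over only one month at month 1. These cannot simply be re-based.

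**Conclusion.** The point holds in a limited form and should be fixed. The ED anchor conflicts with a trial that selects and randomises at month 1. The consequence for the arm comparison is imprecision, and dilution of the yes/no criteria by declines that treatment could not have prevented. It is not bias. Hypothesis 2, a within-cohort comparison, is affected directly, since one of its four months precedes the trial.

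For the SF12 mental criterion, about 25% to 33% of RCT participants would meet it at randomisation and 67% to 75% could never meet it. These figures assume r of 0.7 to 0.5, normal scores and one common cut, and they illustrate rather than estimate. The Aim 2a overlap is confined to the mental half of one criterion among eleven. The physical half of the SF12 rule and the other ten criteria are not circular, although they share the early anchor.

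**What to change.** 1. For the RCT and Hypothesis 2, name the month-1 telephone measurement as baseline for the scored and status measures (ADL, iADL, SF12, AQoL, gait aid, living arrangements, carer and community supports), and compare arms with a model adjusted for it.
2. Analyse falls and hospitalisations as rates after randomisation, adjusted for the pre-recruitment history taken in the ED.
3. In the RCT, replace the SF12 median-crossing rule with MCS and PCS as continuous scores. Re-basing the rule is not enough (Step 6).
4. For Aim 2a, count FD only after month 1 and leave the MCS criterion out of the outcome.
5. State which median any remaining SF12 criterion uses.

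The cost is a change of analysis wording. Table 1 already schedules every listed measure at month 1, so no visit or instrument is added. The falls and hospitalisation analyses need their own specification because of the short month-1 look-back.

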### Baseline screening

We will collect data in the ED (baseline) on consenting, eligible participants from

•the electronic hospital admissions system - age, gender, residential details, differential diagnosis; and

•a test battery as successfully piloted in our 2011 study [37]. This captures the highest level of schooling, primary language, ED presentations and hospitalizations in the past six months, falls in the past twelve months using the Falls Risk in Older People - Community (FROP_COM) instrument [39], living arrangements, requiring a carer, receiving community services, type and use of gait aid, iADLs[19] and cognition with the Mini Mental State Examination (MMSE) [40].

Based on data from our pilot study, we will additionally apply the Katz *et al*. [18] 20 basic ADL instrument and two quality of life measures – the SF12 [41,42] and the Australian Quality of Life (AQoL 4D) [43]. By collecting both basic and iADL scores, we can provide comprehensive ADL information about the target population to compare with international data. The SF12 provides the opportunity for international population-based comparisons of quality of life [41,42] with our sample of older ED presenters. The AQoL, which has not previously been used for older people discharged from ED, provides an Australian perspective on health-related multi-attribute utility quality of life [43], and allows production of health cost effectiveness data (quality-adjusted life years (QALYs)), and estimation of burden of disease.

This total test battery takes an average of 5.5 minutes to administer. All but two questions are delivered verbally by the recruiting researcher, who records the answers. The older person only has to write responses to two MMSE questions.

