### Outcome measures

At one, four, seven and thirteen months after recruitment, all participants will be contacted by telephone and consent sought for interview. Socio-demographic information will be confirmed, and all outcome instruments and mutable independent variables will be recorded (Table 1). Semi-structured questions will be asked about how participants are managing, their concerns and reasons for subsequent hospitalizations and ED presentations. At the four, seven and thirteen month data collection points (after nested RCT commencement), assessors will be blinded to group allocation.

**Table 1 T1:** Timeframes of outcome measurements

**Measures**	**Baseline**	**1 month**	**4 months**	**7 months**	**13 months**
ADLs	√	√	√	√	√
iADLs	√	√	√	√	√
SF12	√	√	√	√	√
AQoL_4D	√	√	√	√	√
Falls	√ (last 12 months)	√ (last month)	√ (last 3 months)	√ (last 3 months)	√ (last 6 months)
Hospitalizations	√ (last 6 months)	√ (last month)	√ (last 3 months)	√ (last 3 months)	√ (last 6 months)
Gait aid (type)	√	√	√	√	√
Living arrangements	√	√	√	√	√
Carer engagement	√	√	√	√	√
Organized (formal) community services	√	√	√	√	√
GP visits	√	√	√	√	√
Informal community supports	√	√	√	√	√
Satisfaction with community supports	√	√	√	√	√

ADLs, activities of daily living; AQoL_4D, Australian Quality of Life; GP, general practitioner; iADLs, instrumental activities of daily living; SF12, Short Form-12 Health Survey; √ indicates an occasion of data collection.

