### Hypotheses

As shown in Figure 2, our hypothese are:

1. The observed cohort will not demonstrate FD over the following 12 months in any FD measure.

2. The low SF12-MCS, no treatment cohort will demonstrate significant FD in any one or more outcome measures, taken over the next three months, when compared to their baseline recruitment status.

3. The low SF12-MCS, intervention cohort will show no FD (comparable findings to the observed cohort) over the next 12 months.

4. Additionally, those individuals in the low SF12-MCS, no treatment cohort who demonstrate significant FD at three months follow-up, and who access ‘rescue’ intervention (see Section on Ethics), will show an attenuated rate of FD over the following twelve months, compared with the rate they exhibited in the first three months.

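### Functional decline is declared on any fall in AQoL_4D with no minimum change stated, so measurement noise alone can flag up to half of stable participants at a single contact

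*Protocol article*

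**What the plan says.** The Study 1 analysis section opens with "FD will be assessed as change from baseline at each time point as" and then gives eleven criteria. The AQoL criterion is "Any decrease in AQoL_4D"; with its reference, the bullet reads "Any decrease in AQoL_4D (in the manner recently described for chronic obstructive pulmonary disease (COPD))[44". It gives no size for the fall; whether the cited COPD source supplies one cannot be seen here. The iADL bullet does set a size for the total score: "Decrease of 2+ points from baseline total iADL score".

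AQoL_4D is collected at baseline in the emergency department (ED) and at four follow-ups: "At one, four, seven and thirteen months after recruitment, all participants will be contacted by telephone". Three of these come after randomisation. The Baseline screening section describes the instrument as new to this setting: "The AQoL, which has not previously been used for older people discharged from ED". The article gives no reliability, standard error of measurement or important difference for it.

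The Hypotheses section uses FD in absolute terms. Hypothesis 1 is that "The observed cohort will not demonstrate FD over the following 12 months in any FD measure". Hypothesis 2 is met by significant FD in one or more measures in the untreated low-score cohort, Hypothesis 3 expects none in the intervention cohort, and Hypothesis 4 concerns untreated participants who show FD at three months and then take up rescue care. The Ethical issues section lets possible FD on a single measure prompt a suggestion of rescue care in the two cohorts that receive no intervention.

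**The concern.** A repeat measurement on a person who has not changed will fall below the first one about as often as it rises above it. A cut at zero therefore reads ordinary measurement variation as decline. With no ties the false rate does not depend on how precise the instrument is, because any error at all puts a zero cut inside the noise.

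The AQoL criterion can count alone, since the hypotheses and the Ethical issues section refer to any one measure. If FD is counted per person:

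- Hypothesis 1 and the no-FD part of Hypothesis 3 can fail although nobody declined.
- Hypothesis 2 becomes easy to satisfy.
- Hypothesis 4 can succeed without any effect of rescue care, because people selected for a low three-month score tend to drift back up.
- The flag used in the Ethical issues section would include many stable participants in the untreated cohorts.

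**Working it through.** **Inputs from the protocol article.** The cut is any fall from one baseline score, judged at each contact. There are k = 4 follow-ups, of which k = 3 are after randomisation, and 50 participants per randomised arm (Sample size considerations). The article states no AQoL_4D error or expected FD rate, and its sample size rests on iADL and SF-12, so it has no figure of its own to reproduce on this point.

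**Assumptions, not in the article.** The true score is constant, with independent errors of equal variance at every occasion.

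**1. One contact.** P(follow-up below baseline) = (1 − proportion tied)/2.
- No ties: 50%. Ties of 10%: 45%. Ties of 20%: 40%. Ties of 40%: 30%.

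**2. Any of k contacts.** With no ties, baseline is the lowest of k + 1 exchangeable scores with probability 1/(k + 1), so P(at least one fall) = k/(k + 1).
- k = 3: 3/4 = 75%. k = 4: 4/5 = 80%. Simulation of 400,000 subjects agrees.

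**3. Sensitivity.**
- Assumed ceiling at 1.00, rounding to 0.01, true mean 0.75, SD 0.20, error SD 0.05 to 0.10: 43–45% at one contact and 67–70% over three.
- Assumed reliability 0.70–0.95 and score steps of 0 to 0.5 SD: about 24–50% at one contact, 42–75% over three and 47–80% over four. Over several contacts, only the coarsest score at reliability 0.95 falls below half.
- Depressed ED baseline, assuming recovery of 0.05 and error SD 0.07: the SD of change is 0.07 × √2 = 0.099, so P(fall) = Φ(−0.05/0.099) = Φ(−0.505), about 31%. A shift in the other direction between the ED and telephone interviews would raise the rate.

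**4. With a margin of 1.96 × √2 × SEM** (SEM is the standard error of measurement). The SD of change is √2 × SEM, so P(false flag) = Φ(−1.96) = 2.5% at one contact. Simulation without ties gives about 6% over three contacts and 8% over four. With the coarse scores of step 3, the three-contact figure ranges from about 3% to 13%.

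**5. Regression to the mean in Hypothesis 4.** Take normal errors, no true change, and people selected because the three-month score is below baseline. The expected fall is √2 × SEM × √(2/π) = 1.13 SEM. By symmetry half of it comes from a low three-month error, so the expected change from there to the next contact is a rise of 0.56 SEM. An apparent decline followed by apparent recovery appears with no rescue effect.

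**6. Effect on the randomised comparison.** Assume a true difference of 0.56 SD of change and n = 50 per arm.
- Means: Φ(0.56 × √(50/2) − 1.96) = Φ(0.84) = 80% power.
- Any fall, yes/no: 50% against Φ(−0.56) = 28.8%, which gives 59% power.

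**The case against.** **The cited method may contain a threshold.** This stands as a limit on what can be said: the defect is that this text states no minimum, not that none exists. If the source has one, the words as printed misstate it; if it has none, the problem remains. The wording needs attention in either case.

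**A reader might infer that most stable participants are misclassified.** The article does not support this at a single contact, and it assesses FD at each time point. Under the exchangeable model the ceiling there is 50%, and ties or a depressed ED baseline bring it lower. The 75% and 80% figures require counting a fall at any contact, a rule the article does not define, although the 12-month wording of Hypotheses 1 and 3 invites it.

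**A reader might infer that the FD hypotheses cannot be read at all.** That goes too far. The section on analysis of Studies 1 and 2 models each outcome over time by cohort with repeated measures ANOVA, which does not use the cut. The hypotheses are phrased about cohorts, and symmetric noise gives zero mean change, so Hypothesis 1 can hold when read that way. The other ten criteria can be reported separately. Similar noise in both randomised arms costs power and does not create a difference.

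**A reader might extend the point to "Decrease of one point in any item of the ADL instrument".** This is not supported. The article gives no misreport rate for ADL items, a one-point item loss can be a real and discrete loss of function, and a net total could hide it behind a gain elsewhere.

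**Conclusion.** The concern holds for the AQoL_4D criterion as printed. With no minimum change, it flags up to 50% of truly stable participants at one contact, and up to 75% (three contacts) or 80% (four contacts) if a fall at any contact counts. These are modelled upper figures under exchangeable errors and no ties, since the article reports no AQoL_4D measurement error.

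The damage is confined to participant-level use of FD: Hypotheses 1 to 4 when read per person, and the single-measure flag in the Ethical issues section. The mean comparisons stand. A yes/no comparison of the randomised arms on this criterion would be weakened rather than lost.

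**What to change.** In the Study 1 analysis section, replace the zero cut for AQoL_4D with a fall larger than a stated margin, fixed before any data by arm are seen. Use the threshold in the cited COPD method if it sets one. Otherwise use, for example, 1.96 × √2 × SEM, naming the source of the SEM.

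Alternatively, take AQoL_4D out of the yes/no FD rule and compare it between the randomised arms as a continuous outcome, which the planned repeated measures model already comes close to doing.

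Because the Ethical issues section draws on the same flag, it must be reconciled with whichever definition is adopted. No view is offered here on when rescue care should be suggested.

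The cost is a change of wording and no new data. The downside is that very small true utility losses no longer count as FD for an individual, though they still contribute to the comparison of means. The ADL criterion needs no change on this ground.

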### The intervention

The intervention arm applies a novel person-focused home-based approach targeting individual need [45]. Patient/person-centered care has been defined by Berwick [46] as ‘The experience (to the extent the informed, individual patient desires it) of transparency, individualization, recognition, respect, dignity, and choice in all matters, without exception, related to one’s person, circumstances, and relationships in health care’ [46],p2].

The intervention will be applied independently by a large provider of community aged care in South Australia (Elderly Citizens Homes (ECH)). This group has developed a patient-centered program for community-dwelling older individuals considered by their GP to be at-risk of declining functionally. The program involves a home assessment and interview conducted by occupational therapists or physiotherapists to identify individual problems and concerns and to set appropriate goals. Care options are discussed with older people and families in particular individualized interventions, which could include attendance at day therapy centers, exercise, fitness, balance-retraining and/or socialization, organization of home help or community care packages, motivational interviewing or counseling. Transport to programs can also be provided to increase compliance and reduce attendance barriers. Programs can last three to fourteen weeks, depending on need. The median/person cost of the intervention approximates $2,100 (interquartile range (IQR) $350), which approximates the cost of one acute South Australian hospital bed-day.

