### Ethical issues

Written permission has been obtained from the Hospital Executive and ED Management of the research site, and ethical approval has been granted by the Human Research Ethics Committee of the University of South Australia (Application ID: 0000031475).

While there are indications from its early evaluation data that the ECH intervention is acceptable to clients, its effectiveness is largely unproven, particularly in individuals with low SF12-MCS scores at commencement. We do not know that the intervention will provide any advantage; in fact, individuals may perceive that they are subjected to additional burdens, such as unwanted assessments and visitors in their home for (perhaps) no overall benefit. We see no disadvantage for the ‘control’ group (low SF12-MCS, no treatment cohort) at this point in our understanding, in not being offered care, nor not knowing that the intervention is available, as they are currently not offered routine intervention so early after an ED discharge. If ,however, at subsequent follow-up points (three, six or twelve months), any participant in the observed cohort arm or the low SF12-MCS, no treatment arm is identified as potentially demonstrating FD on any study measure, the need for rescue care will be suggested and ways to access this discussed. This may include attendance at their GP or making contact with local community service providers.

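### The functional-decline criteria on community services and GP visits can score care arranged by the programme, or taken up as rescue, as decline

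*Protocol article*

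**What the plan says.** All places are in the protocol article.

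- **Study 1 analysis** opens its list of criteria with "FD will be assessed as change from baseline at each time point as". The list includes "Greater type and frequency of use of formal community services or informal supports", "Increased carer involvement" and "More frequent GP attendances", alongside falls, hospitalizations, ADL, iADL, SF12, AQoL_4D, gait aid and living arrangements.
- **Study 1: Longitudinal cohort study** places the whole sample in Study 1 and has every participant assessed for FD. Table 1 (Outcome measures) records formal services, informal supports and GP visits at all five contacts.
- **The intervention** lists what a programme could contain. Day therapy centres and exercise are among the options, as is "organization of home help or community care packages, motivational interviewing or counseling". A programme lasts 3 to 14 weeks.
- **Subject selection and randomization** sets the RCT assessments at 3, 6 and 12 months after randomization.
- **Ethical issues** provides that, at those follow-ups, observed or no-treatment participants who may be showing FD on any measure have rescue care suggested to them: "This may include attendance at their GP or making contact with local community service providers".
- **Hypotheses** predicts no FD in the intervention cohort, comparable with the observed cohort (Hypothesis 3). It predicts a slower rate of FD after rescue in controls who declined by three months (Hypothesis 4).

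**The concern.** Some FD criteria measure receipt of care, and both the programme and the rescue advice can deliver that care. Baseline is the emergency department visit, before randomization, so a service arranged afterwards is an increase from baseline whatever the person's function. The same event is then both the treatment and the sign that treatment failed.

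Hypothesis 3 could fail, at least in part, because the programme was delivered. Hypothesis 4 could fail because rescue was taken up. The two distortions act in different arms and at different times, so their net effect on a later comparison between arms cannot be predicted. Blinding the assessors does not help, because the item correctly records a real rise in service use.

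**Working it through.** **Step 1. Does the list reach the randomized arms?** It stands under a Study 1 heading, but Study 1 contains every participant, Table 1 collects the items at every contact, and the hypotheses speak of FD in all three cohorts. It does.

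**Step 2. Does the timing allow overlap?** Three months is about 13 weeks and a programme can run to 14, so it can still be running at the first RCT visit. By 6 and 12 months the programme itself is over. Only home help or a care package that continues afterwards could still count, and the documents do not say how long such services last.

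**Step 3. Which item is tied to which care?**

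| FD item | Programme | Rescue |
|---|---|---|
| Formal community services | yes, as an option | yes, as an option |
| GP attendances | not stated | yes, as an option |
| Carer involvement | not stated | not stated |

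**Step 4. In what order do things happen?** Rescue is suggested only after a possible FD flag, at the three-month follow-up at the earliest. It cannot cause the first flag and does not touch Hypothesis 2, which concerns the first three months. It can add or prolong flags at 6 and 12 months, the period in which Hypothesis 4 expects FD to slow.

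**Step 5. How large could it be?** The plan gives no figure for this and no rate of service uptake, so what follows is illustration only.

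Inputs:
- n = 50 per arm and α = 5%, from Sample size considerations; sidedness is not stated and two-sided is assumed. The 50 cannot be reproduced because no SD is given. Solving backwards, SD = 1.2 / [(1.960 + 0.842) × √(2/50)] = 2.14. The point does not depend on it.
- Control FD pc = 50%, borrowed from the likelihood of FD at discharge in Pilot work underpinning this protocol. It is not an observed three-month rate.
- True intervention FD pt = 20%, 25% or 30%: assumed.
- q = share of non-declining intervention participants flagged only for arranged services: assumed.

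Observed intervention FD: po = pt + (1 − pt) × q.

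Power = Φ{[|pc − po| − 1.96 √(2p̄(1 − p̄)/n)] / √([pc(1 − pc) + po(1 − po)]/n)}, where p̄ is the mean of pc and po.

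Example, pt = 0.20 and q = 0.2: po = 0.20 + 0.80 × 0.2 = 0.36 and p̄ = 0.43. Power = Φ[(0.14 − 1.96 × 0.0990)/0.0980] = Φ(−0.55) = 0.29.

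| pt | Power, q = 0 | q = 0.1 | q = 0.2 | q at which the benefit vanishes, (pc − pt)/(1 − pt) |
|---|---|---|---|---|
| 20% | 89% | 62% | 29% | 0.30/0.80 = 0.375 |
| 25% | 74% | 43% | 17% | 0.25/0.75 = 0.333 |
| 30% | 53% | 26% | 9% | 0.20/0.70 = 0.286 |

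Above the last column, the intervention arm appears to decline more than control.

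For the service item alone, suppose 50% of the intervention arm and 20% of controls gain a service. The same formula gives about 89% power to find more FD on intervention, by 50 − 20 = 30 points.

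**The case against.** The strongest reply is that the trial does not stand or fall on a composite. Analysis of data from Studies 1 and 2 models each outcome separately, and Sample size considerations sizes the RCT on iADL, using a drop of two or more points on the Lawton scale as FD. Neither depends on care received. This stands, and it sets the limit of the point. The table above applies only if FD is judged on any one measure, as the wording of Hypotheses 1 and 2 suggests; Hypothesis 3 says only that there will be no FD.

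A reader might also infer more than the text supports:

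- **That everyone treated as planned meets FD.** The services are options, and a programme could consist of exercise or counselling instead.
- **That rescue creates decline in controls.** It follows a flag and is only suggested.
- **That the carer item is equally affected.** No section says that the programme or rescue supplies a carer.
- **That "Any decrease in AQoL_4D" mislabels many stable people.** That criterion goes on to refer to a published method for chronic obstructive pulmonary disease, which cannot be seen here and may set a threshold. No claim about measurement noise can rest on it.

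One might add that a real rise in need also raises service use, so the item carries some information. It does, but in the randomized comparison that information cannot be separated from delivery of the programme.

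**Conclusion.** The concern holds in a limited form. Applied as written, the formal-services criterion can score programme-arranged care as FD, most directly at the three-month RCT visit, and this works against Hypothesis 3. The service and GP criteria can score rescue as FD at later visits. That works against Hypothesis 4 and distorts later comparisons with the untreated cohorts.

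What is affected is the service and GP items and any FD verdict reached on any single measure. It would be wrong to conclude that the trial's functional results are contaminated: the ADL, iADL, falls and SF12 analyses do not count receipt of care.

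The size is unknown. The figures of 29% to 38% and the loss of power rest on a borrowed control rate, assumed true rates and a binary any-measure comparison. They show that moderate overlap would be enough to matter, not that it will occur.

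**What to change.** For the randomized comparison and for Hypotheses 3 and 4, define FD from the functional measures, ADL and iADL, and report falls and hospitalizations separately. Report formal services, informal supports and GP attendance as service-use or cost outcomes. If they must stay among the FD criteria, state at the least that care arranged by the programme or taken up as rescue is not counted as FD.

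The main change is one of wording and uses data already collected at every contact. The fallback also needs the source of each service to be recorded at interview. The price is a narrower definition of FD for the RCT than the list under Study 1 analysis. The full list can still be used to describe the cohort.
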